3.1. People in training/education

3.2. Pensioners

3.3. Other not economically active

### Inclusion criteria

A person will be included in the study if he/she

1. on at least one occasion in the time period 1996 - 2006, was registered in the hospital patient registry with one of the following ICD-10 codes as principal diagnosis:

• I60 subarachnoid haemorrhage

• I61 intracerebral haemorrhage

• I63 cerebral infarction

• I64 stroke, not specified as haemorrhage or infarction

2. belonged to the age interval 20 - 57 years at the time of the hospital contact

3. was gainfully occupied the year preceding the hospital contact

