### Statistical analysis

The study will consist of two parts, one is descriptive while the other utilises statistical inference techniques to test hypotheses and estimate odds ratios for RTW (return to work).

In the descriptive part we follow the stroke patients for five calendar years after the stroke and register their main social status in each of these years. This part of the study will only include people who were less than 55 years at the time of the stroke. For any given patient, the calendar year of the stroke will be defined as year 0, the next calendar year will be defined as year 1 etc.

In the regression analysis, we will look at the odds of having a socio-economic code, which indicates gainful occupation in year 2 after stroke. The outcome variable is set to 1 if the person is self-employed, assisting spouse or employee in that particular year. It is set to 0 if the person is unemployed, not economically active or dead.

As explanatory variables we will use gender, age, diagnosis, calendar year, occupational class, self-employment, and type of municipality.

Age at the time of the stroke will be divided into the categories 20 - 49 years and 50 - 57 years. In Denmark it is possible to retire at the age of 60, regardless of health condition. This is why we do not include people who would be older than 60 years at follow-up. The cut-point 50 years conforms to OECD's definition of older workers [13], who are known to have a more insecure labour market attachment than the younger ones.

The variable 'Diagnosis' contains the four stroke categories given in the section 'inclusion criteria'.

The variable 'Self-employment' is set to 1 if the person is self-employed or assisting spouse and 0 if he/she is an employee, the year preceding the stroke.

The variable 'Occupational class' is based on the first digit of the DISCO-88 classification the year preceding the stroke. It contains the following categories:

• Legislators, senior officials and managers (DISCO-88 group 1)

• professionals (DISCO-88 group 2)

• technicians and associate professionals (DISCO-88 group 3)

• workers in occupations that require skills at a basic level (DISCO-88 group 4 - 8)

• workers in elementary occupations (DISCO-88 group 9)

• gainfully occupied people with an unknown occupation (missing DISCO-88 code)

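### The age limits do not quite keep retirement at 60 out of the outcome, because age is fixed at the hospital contact while status is read over a whole calendar year

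*Protocol article*

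**What the plan says.** Under Inclusion criteria, a person qualifies who "belonged to the age interval 20 - 57 years at the time of the hospital contact". Under Statistical analysis, the reason for the upper limit is that "In Denmark it is possible to retire at the age of 60, regardless of health condition", followed by the rule "This is why we do not include people who would be older than 60 years at follow-up".

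The descriptive part has a lower limit: "This part of the study will only include people who were less than 55 years at the time of the stroke".

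The follow-up clock runs in calendar years: "the calendar year of the stroke will be defined as year 0, the next calendar year will be defined as year 1 etc". The regression models "the odds of having a socio-economic code, which indicates gainful occupation in year 2 after stroke". The descriptive part reads status annually: "we follow the stroke patients for five calendar years after the stroke and register their main social status in each of these years". For the regression outcome, "It is set to 0 if the person is unemployed, not economically active or dead". The social classification under Methods/design lists pensioners among the not economically active. The Discussion confirms that the register holds only a person's main occupation and social group for each calendar year.

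**The concern.** If retirement is open to anyone at 60, keeping it out of the outcome requires that nobody is 60 at any point in the year when status is read. The limits are set in completed years at the contact, so they bound age at the anniversary of the stroke. They do not bound age through the calendar year that supplies the outcome.

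Someone who leaves work at 60 for reasons unrelated to the stroke can then be counted as a failure to return to work. In the regression every such person is in the 50-57 category and none is in the reference category. The error therefore runs one way, and a large sample does not reduce it. It touches the age odds ratio in Table 2, the group proportions that the Discussion offers municipalities as comparison material, and the pensioner row of Table 1.

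**Working it through.** **Inputs from the protocol article.** Upper age 57 completed years at contact (regression) and 54 (descriptive); stroke year is year 0; outcome read in calendar year 2 (regression) and years 1 to 5 (descriptive); retirement possible at 60; status is the main one of the year; older category 50-57.

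**Assumptions (the document gives no figures).** Stroke date and birthday independent and uniform over the year; main status means more than half the year; case numbers rise by 0% to 12% per year of age; 50% return rate in the older group; 25% to 100% of those exposed who would otherwise be working retire.

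**1. The limit as the plan appears to intend it.** At the exact two-year anniversary the oldest participant is 57.99 + 2 = 59.99. On that clock nobody is 60 and the limit works.

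**2. The limit on the calendar-year clock.** A person aged 57 at a stroke in year Y was born in Y − 57 (birthday already passed) or Y − 58 (birthday still to come). The second kind turns 60 in Y − 58 + 60 = Y + 2, which is the outcome year. Age at the end of year 2 runs from 59.0 to 60.99, so nobody reaches 61.

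**3. How many 57-year-olds.** Let U be the stroke date and B the birthday, each as a fraction of the year.
- Turn 60 in year 2: P(B > U) = 0.50.
- Aged 60 for more than half of year 2: P(U < B < 0.5) = 0.5² / 2 = 0.125.

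A simulation gave 0.500 and 0.125.

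**4. Share of the 50-57 group.** With growth g per year of age, 57-year-olds make up s = (1 + g)⁷ / Σ(1 + g)ᵏ, k = 0 to 7.

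| g | s | turn 60 in year 2 (0.5 s) | 60 for most of it (0.125 s) |
|---|---|---|---|
| 0% | 12.5% | 6.3% | 1.6% |
| 5% | 14.7% | 7.4% | 1.8% |
| 8% | 16.1% | 8.1% | 2.0% |
| 12% | 18.0% | 9.0% | 2.2% |

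**5. Effect on the older group's odds.** With return rate p = 0.50 and uptake r, the observed rate is p(1 − 0.125 s r).
- g = 0%, r = 25%: 0.4980, odds multiplied by 0.992.
- g = 8%, r = 50%: 0.4950, odds multiplied by 0.980.
- g = 12%, r = 100%: 0.4888, odds multiplied by 0.956.

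The under-50 group is untouched: a 49-year-old is at most 52.99 at the end of year 2. The age odds ratio therefore moves by the same factor.

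**6. Descriptive part.** A 54-year-old is at most 57.99 at the end of year 2, 58.99 at the end of year 3, 59.99 at the end of year 4 and 60.99 at the end of year 5. Only year 5 is exposed, with the same 50% and 12.5%. For g = 6% to 10%, 54-year-olds are about 6.5% to 9.4% of the 20-54 cohort. About 0.8% to 1.2% of the cohort (0.125 × 6.5% to 0.125 × 9.4%) is then 60 for most of year 5, before allowing for uptake.

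**7. Check of the remedy.** If stroke year minus birth year is at most 57, the age attained in year 2 is at most 59. If it is at most 54, the age attained in year 5 is at most 59.

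**The case against.** The strongest reply is that the rule, as worded, is kept. In completed years nobody is over 60 at follow-up. The Abstract places follow-up at about two years after the stroke, and at the exact anniversary nobody has even turned 60. This stands: a reader might infer that the limits contradict the exclusion sentence itself, and in completed years they do not. What remains is that the limits fall short of the reason given for them, because status is read over calendar year 2 and not at the anniversary.

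Three other stronger readings are tempting and are not supported:

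- **That everyone who reaches 60 is counted as not returned.** The coding depends on main status. A 60-year-old who keeps working is coded 1, and so is one who retires late in the year. Only people who retire early enough, and who would otherwise have been working, change the outcome.
- **That 6% to 9% of the older group is affected.** That is the share turning 60 at any time in year 2. Under the main-status rule the exposed share is about 2%.
- **That the year-2 pensioner percentage is inflated.** Pensioner percentages appear only in Table 1, which covers ages 20-54, so nobody in its year-2 column can be 60.

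It is also fair to say that the protocol does not present the age odds ratio as a pure health effect. It justifies the cut at 50 by older workers' weaker attachment to the labour market. That lowers the stakes, but the protocol still set the upper limit to deal with retirement at 60.

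**Conclusion.** The point holds as a minor flaw. The age limits do not fully achieve their stated purpose in either part of the study. In the regression about 2% of the 50-57 group is exposed, and that group's odds of return are biased downward by a factor of roughly 0.96 to 0.99. The lower end requires every exposed person who would otherwise work to retire. In Table 1 only the year-5 pensioner percentage can be inflated, by at most about one percentage point.

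The calendar arithmetic follows from the document alone. The sizes rest on the assumed uniform dates, age gradient, 50% return rate and retirement uptake. The case for acting is that the bias runs in one direction and is easily avoided, not that it is large.

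**What to change.** Keep the stated age ranges and add a condition on the age attained in the outcome year: stroke year minus birth year at most 57 for the regression, and at most 54 for the descriptive part. Reword the justification so that it excludes people who would reach 60 by the end of the outcome year. Birth dates are already in the central person register, so no new data are needed.

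**Cost.** The rule drops about half of the 57-year-olds. With an age gradient of 6% to 10% per year (assumption), 57-year-olds are about 6.4% to 9.3% of the 20-57 cohort, so roughly 3-5% of the regression sample is lost. This includes people whose outcome would not have been affected, since only about a quarter of those dropped (0.125 / 0.50) would be 60 for most of year 2. The descriptive cohort loses about 3% to 5% likewise (half of 6.5% to 9.4%).

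**Power.** For self-employment, the plan's inputs give SE = √[1.2 × (1/(2000 × 0.55 × 0.45) + 1/(18000 × 0.55 × 0.45))] = 0.0519 and power of about 99.9% at an odds ratio of 1.3. With 19,000 people and the same 10% share, the SE is 0.0519 × √(20/19) = 0.0532 and power is still about 99.8%, above the stated 95%.

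If the sponsor prefers to keep the full cohort, the same restriction could be reported as a sensitivity analysis. The main estimate would then keep the small bias.

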The variable 'Type of municipality' is set to 1 if the person lived in a municipality which had a brain injury rehabilitation centre at the time of the stroke. Otherwise it is set to 0. The following municipalities had a brain injury rehabilitation centre throughout the study period: Copenhagen, Odense, Aarhus, Roskilde, Aalborg and Vejle.

There are at least two reasons for believing that the RTW probabilities depended on which calendar year the stroke occurred. Firstly, quality of stroke treatment and rehabilitation has a tendency to improve with time. This is illustrated by two Finish studies which show that 28-day case fatality rates among 35 - 74 year-old stroke patients decreased by approximately three percent annually in the time period 1983 - 2001 [14,15]. A similar trend was observed in England [16]. Secondly, a series of political initiatives and legislative changes, aimed at improving return to work rates in Denmark, occurred during the study period. In 1998, the flexi-job system was introduced, which allows people with permanently reduced work capacity to work part time, yet through public subsidy get full salary. In 2001, the flexi-job system was reformed. A person who is eligible to a flexi-job would be entitled to unemployment benefits if no such work could be found. In 2003, a new disability retirement scheme was introduced. The main intent of the reform was to ascertain that as many as possible retain their attachment to the labour market. A new procedure for assessing work capacity was introduced, and disability pension would only be granted if work ability was permanently reduced and flexi-job work was unfeasible. In 2005, the municipal control of the sick-listed was intensified by a change in the Sickness Benefit Act. Follow-up evaluations were required once a month instead of once every second month, and a reintegration plan was to be drawn up after four instead of six months [17]. To deal with this possible time dependency, we incorporate calendar year into the model as a class variable.

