It is also reasonable to believe that RTW probabilities depend on place of residence. In Denmark, municipalities play an important role in the return to work process. According to the law, it is the municipal officer and not the physician who has the formal right to decide whether or not a person qualifies for sickness benefit, disability pension, or vocational rehabilitation. The law also stipulates that the municipality should perform regular follow-up evaluations and draw up detailed reintegration plans for each sick-listed citizen at risk of long-tem sickness absence [17]. RTW initiatives are often launched at the municipality level and some municipalities might be more active than others. The unemployment situations may also differ between municipalities. In the present study, we will use a multi-level analysis to deal with intra-municipality correlations -- the municipalities are treated as the subjects while the individual observations within the municipalities are treated as correlated repeated measurements.

The logistic regression will be performed by use of the GENMOD procedure in SAS version 9.1. Only main effects are considered. An exchangeable correlation structure is assumed. The empiric standard error estimates will be used.

Table 1 shows how the results from the first part of the study will be presented. Table 2 will list odds ratios and P-values that will be estimated in the second part of the study. Odds ratio for return to gainful occupation two year after stroke, by onset calendar year, will be illustrated by a graph. The calendar year 1996 will be used as reference. All hypotheses are two-tailed. A P-value will be deemed statistically significant if it is less than 0.05.

**Table 1 T1:** Social group distribution (%) by time passed since onset of illness, among stroke patients in Denmark who were 20-54 year of age and gainfully occupied at the time of the stroke

Social status	Year after stroke				
	1	2	3	4	5
Self-employed people					
Assisting spouses					
Employees					
People on unemployment benefits					
People in training/education					
Pensioners					
Other not economically active					
Deceased					

Total	100	100	100	100	100

**Table 2 T2:** Odds ratios (OR), with 95% confidence interval (CI) for return to gainful occupation two year after stroke

Parameter	Level	N	OR	95% CI
Gender (P = xxx)	Men		1.00	-
	Women			
Age (P = xxx)	<50 years		1.00	-
	50 - 57 years			
Diagnosis (P = xxx)	Subarachnoid haemorrhage			

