Another limitation of the study concerns the variable 'municipality type'. The study can tell us whether or not stroke patients in municipalities with brain injury rehabilitation centres have a better prognosis than those in other municipalities but it cannot tell us if this is due to the centres. That question can only be answered through a randomised study.

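### Local unemployment, which the protocol says may vary by municipality, is handled only through the correlation structure and so can enter the municipality-type odds ratio; a second, adjusted row would be a cheap improvement

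*Protocol article*

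**What the plan says.** All places are in the protocol article.

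- **Exposure (Statistical analysis).** "The variable 'Type of municipality' is set to 1 if the person lived in a municipality which had a brain injury rehabilitation centre". Residence is judged when the stroke occurs, and everyone else is coded 0. The centre group is listed by name: "Copenhagen, Odense, Aarhus, Roskilde, Aalborg and Vejle", each with a centre for the whole study period.
- **Model terms (Statistical analysis).** "As explanatory variables we will use gender, age, diagnosis, calendar year, occupational class, self-employment, and type of municipality". None of the seven measures the local labour market.
- **Why residence matters (Statistical analysis).** Several reasons are given: the municipal officer's decision powers, follow-up duties, varying local initiatives, and "The unemployment situations may also differ between municipalities".
- **The response (Statistical analysis).** "we will use a multi-level analysis to deal with intra-municipality correlations", fitted in GENMOD. "An exchangeable correlation structure is assumed", and empirical standard errors are used.
- **Outcome (Statistical analysis).** Self-employed people, assisting spouses and employees in year 2 are coded 1. Unemployed, inactive and deceased people are coded 0.
- **Reporting (Table 2).** Municipality type has its own P-value, odds ratio and 95% confidence interval.
- **Interpretation (Discussion).** The study is said to be able to show whether "stroke patients in municipalities with brain injury rehabilitation centres have a better prognosis than those in other municipalities", but not whether the centres are the reason. That question is left to a randomised study.

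**The concern.** The protocol gives two parallel reasons for expecting return to work to vary: calendar time and place of residence. It deals with calendar time by putting calendar year into the model as a class variable, so that it is adjusted for. It deals with residence through the correlation structure. For patient-level predictors that may be enough. Municipality type, however, is itself a municipality-level predictor with a tested odds ratio, and a possible municipality-level explanation for it is left outside the mean model.

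The outcome is sensitive to that explanation. A patient who is fit to work but cannot find a job locally is coded the same as one who has not recovered. If jobs were systematically easier or harder to find in the six municipalities, the row could depart from 1 with no difference in recovery or rehabilitation. A reader of Table 2 could not tell the two apart, although the register appears to hold what is needed to examine this.

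**Working it through.** **1. The plan's own figures.** None is given for municipality type. The only power statement (Power calculations) concerns self-employment: at least 95% power at an odds ratio of 1.3, with about 20 000 patients, 10% self-employed, 55% returning and variance inflated by 20%. Taking 55% as the reference-group rate:

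- effective sizes 2000/1.2 = 1667 and 18 000/1.2 = 15 000
- rates 0.6137 and 0.55
- SE of the log odds ratio = √[1/(1667 × 0.6137 × 0.3863) + 1/(15 000 × 0.55 × 0.45)] = 0.0529
- z = ln(1.3)/0.0529 = 4.96, and power = Φ(4.96 − 1.96) = 99.9%

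The statement holds and is not in dispute.

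**2. What the clustering method does.** The working correlation alters how much weight each municipality carries, and the empirical variance alters the standard error. Neither adds a labour-market term to the mean model. The six named municipalities had a centre throughout the study period, so each is coded 1 in every year, and their contrast with the rest is a between-municipality one. A systematic between-group difference in unemployment would therefore pass into it. Calendar year absorbs national trends but not differences between municipalities in the same year.

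**3. Illustrative size.** The 55% is the protocol's. The other inputs are assumptions: return to work falls by s percentage points per 1-point rise in local unemployment (s = 0.5, 1, 1.5), the two groups differ by u points (u = 1, 2, 4), and there is no other difference between them.

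OR = odds(0.55) / odds(0.55 − s·u/100), where odds(0.55) = 0.55/0.45 = 1.2222.

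| s | u = 1 | u = 2 | u = 4 |
|---|---|---|---|
| 0.5 | 1.02 | 1.04 | 1.08 |
| 1 | 1.04 | 1.08 | 1.17 |
| 1.5 | 1.06 | 1.13 | 1.27 |

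For example, s = 1 and u = 2 give 1.2222/(0.53/0.47) = 1.08. The corner s = 1.5, u = 4 gives 1.2222/(0.49/0.51) = 1.27. If the centre municipalities have the higher unemployment, the inverses apply.

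**4. A second parameterisation.** Assume instead that the odds of return are multiplied by g = 0.99 to 0.95 per point of unemployment, with a difference of d = 1 to 3 points. Then OR = g^d runs from 0.99 to 0.95³ = 0.86 (return to work 54.8% to 51.2% against 55%).

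The chance of P < 0.05 is Φ(z − 1.96) + Φ(−z − 1.96), with z = |ln OR|/SE and the SE formed as in step 1. If 20 to 30% of patients live in the six municipalities (also an assumption), this chance runs from about 6% to over 99% at the protocol's inflation of 1.2. It runs from about 5% to 35% at an inflation of 10. The range is too wide to say more than that the effect could be negligible or visible.

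**5. Can the covariate be built?** The opening of Methods/design describes the linked register as covering everyone economically active and resident in Denmark at some time after 1980, with addresses and annual social status. People on unemployment benefits form social group 2. The elements for a municipality-by-year share are therefore present. The article does not say that such a share has been compiled.

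**The case against.** The strongest reply is that the row is descriptive and the protocol says so. The Discussion lists municipality type as a limitation and declines to attribute any difference to the centres, which covers every non-centre explanation, labour markets included. The outcome is employment status, so the local job market is arguably part of the prognosis being described. This stands: the unadjusted odds ratio is not wrong as a contrast in return to work.

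A reader might infer that the protocol identifies unemployment as a cause of municipal differences, or that the odds ratio is shown to be confounded. The text supports neither. It says unemployment situations may differ between municipalities, and nowhere says that the six differ from the rest. Confounding needs that second link.

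Three further points also stand. The sizes above rest on assumed slopes and gaps, and 1.27 needs both extremes at once. Everyone in the cohort was gainfully occupied the year before the stroke, so they are not general job-seekers. An unemployment covariate also leaves other municipal differences in place, such as officers' decisions and local initiatives, so the existing caveat would still be needed.

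What the reply does not answer is the mismatch between a stated concern about the level of return to work and a remedy that acts on precision. The Discussion's general disclaimer names no labour-market explanation, though this one can be examined without a randomised study.

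**Conclusion.** The point holds in a limited form. The protocol raises possible differences in municipal unemployment and answers with a correlation structure, which cannot keep a systematic difference between the six centre municipalities and the others out of the municipality-type odds ratio. The presence, size and direction of any such difference are not shown. The range 1.02 to 1.27 (or its inverse) is conditional on the assumed inputs and is not an estimate of bias.

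It would be tempting to conclude that the planned row is invalid and should be replaced by an adjusted one. The documents do not support that, because the contrast is presented descriptively and attribution to the centres is already disclaimed. This is an inexpensive improvement to one secondary row of Table 2, not a defect that undermines the study.

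**What to change.** 1. From the Occupational Hospitalisation Register, compute for each municipality and calendar year the share of economically active residents aged 20–57 who are on unemployment benefits: group 2 divided by groups 1 and 2 together.
2. Link it to each patient by municipality of residence at the time of the stroke, for year 0. This matches how municipality type is defined and avoids a labour-market measure taken after the stroke.
3. Keep the planned municipality-type row in Table 2. Add a second row from the same GENMOD model with this share as a continuous covariate.
4. In the Discussion, name local unemployment as one possible explanation of any difference, and read any statement about better prognosis in the light of both rows. Keep the existing caveat on attribution.

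The cost is one derived variable, one extra row and probably a slightly wider interval for the adjusted estimate. No new data collection should be needed.

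### The 95% CI planned for the municipality-type row of Table 2 is too narrow, because an uncorrected empirical standard error is applied to a contrast with only six listed exposed municipalities

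*Protocol article*

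**What the plan says.** All of the following is in the Protocol article, mostly under Statistical analysis.

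- **Exposure.** The indicator for this row "is set to 1 if the person lived in a municipality which had a brain injury rehabilitation centre at the time of the stroke", and 0 in all other cases. The municipalities named are those that "had a brain injury rehabilitation centre throughout the study period: Copenhagen, Odense, Aarhus, Roskilde, Aalborg and Vejle".
- **Clusters.** In the model, "the municipalities are treated as the subjects while the individual observations within the municipalities are treated as correlated repeated measurements".
- **Software and variance.** On software: "The logistic regression will be performed by use of the GENMOD procedure in SAS version 9.1". On the working correlation and variance: "An exchangeable correlation structure is assumed. The empiric standard error estimates will be used".
- **Testing and reporting.** "All hypotheses are two-tailed", at the 0.05 level. Table 2 has a row for municipality type with an odds ratio, a 95% CI and a P-value.
- **Use of the result.** The Discussion claims: "The study can tell us whether or not stroke patients in municipalities with brain injury rehabilitation centres have a better prognosis". It adds that the study cannot attribute a difference to the centres themselves. That caveat concerns causation, not precision.

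No small-sample correction, t reference or remark on the number of exposed municipalities is given. The form of the test behind the P-values is not named.

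**The concern.** The empirical (sandwich) variance is justified when many independent clusters inform each coefficient. Most predictors here vary between patients within a municipality, so the full set of municipalities informs them. Municipality type does not: it compares a handful of municipalities with all the rest. The variance on the exposed side is estimated from as many squared cluster residuals as there are exposed municipalities. Neither 20 000 patients nor a large number of unexposed municipalities adds information there. With so few residuals the sandwich estimate is too small on average and also unstable, so an interval of the estimate plus or minus 1.96 standard errors is too short.

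The Statistical analysis section itself argues that municipalities differ in return-to-work activity and in unemployment. Some chance difference between the centre cities and the rest is therefore to be expected, and the interval in Table 2 is what a reader would use to judge it.

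**Working it through.** **1. The protocol's own figure.** Power calculations gives at least 95% power for a self-employment odds ratio above 1.3 or below 1/1.3. Inputs: N = 20 000, 10% self-employed, 55% returning, variance inflated by 20%, two-sided 0.05.

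- At an odds ratio of 1.3 and 55% overall, the two return rates are about 0.608 (self-employed) and 0.544 (others).
- Var(log OR) = 1.2 × [1/(2000 × 0.608 × 0.392) + 1/(18 000 × 0.544 × 0.456)] ≈ 0.00279, so SE ≈ 0.053.
- ln(1.3)/SE ≈ 0.262/0.053 ≈ 5.0, and power ≈ Φ(5.0 − 1.96) ≈ 99.9%.

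The statement is true and conservative. It concerns self-employment only; the protocol gives no power or error rate for municipality type.

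**2. Where the variance comes from.** With municipality type as the only covariate and working correlation ρ, municipality j has weight w_j = n_j/[1 + (n_j − 1)ρ]. Let p_E and p_U be the weighted return rates in exposed and unexposed municipalities, and ȳ_j the rate in municipality j. The log odds ratio is logit(p_E) − logit(p_U), and its empirical variance is

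Σ_E [w_j(ȳ_j − p_E)]² / [p_E(1 − p_E) Σ_E w_j]² + the same expression for the unexposed.

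With the six listed municipalities, the first term has six squared residuals. On a test dataset this closed form agreed with a standard GEE routine (log OR 0.10086, SE 0.03789 from both).

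Illustration, assuming 98 municipalities, 25% of patients in the six, equal sizes within each group and ρ = 0.005:

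- Exposed: n = 5000/6 ≈ 833, w ≈ 833/5.16 ≈ 161, sum ≈ 969.
- Unexposed: n = 15 000/92 ≈ 163, w ≈ 163/1.81 ≈ 90, sum ≈ 8286.
- Exposed share of the variance ≈ 8286/(8286 + 969) ≈ 90%.

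**3. Limiting case.** If the six dominate and are of equal size, the correct reference is t on 5 df.

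- P(|t5| > 1.96) = 10.7%.
- The sandwich also has expectation 5/6 of the true variance. The effective cut-off becomes 1.96 × √(5/6) = 1.79, and P(|t5| > 1.79) = 13.4%.

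**4. Simulation under no effect.** From the protocol: N = 20 000, 55% returning, six exposed, exchangeable GEE with empirical SE. Assumed: 98 or 275 municipalities; 20-30% of patients in the six; equal, mildly or strongly unequal exposed sizes; beta-binomial clusters; ICC of 0, 0.005, 0.01, or the value that reproduces the protocol's 20% inflation at mean cluster size. That last value is 0.2/(20 000/98 − 1) = 0.00098 or 0.2/(20 000/275 − 1) = 0.00279. There were 20 000 replicates per scenario and municipality type was the only covariate.

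Rejection of a true null (%), 25% of patients exposed, ICC at the 20%-inflation value:

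| Municipalities | Exposed sizes | Wald, empirical SE, 1.96 | Generalised score | Kauermann-Carroll, t5 | Mancl-DeRouen, t5 |
|---|---|---|---|---|---|
| 98 | equal | 9.98 | 4.23 | 2.82 | 2.13 |
| 98 | mildly unequal | 11.57 | 4.57 | 3.69 | 2.84 |
| 98 | strongly unequal | 14.61 | 3.98 | 5.27 | 3.65 |
| 275 | equal | 11.42 | 4.51 | 3.74 | 2.82 |
| 275 | mildly unequal | 12.10 | 4.55 | 4.15 | 3.23 |
| 275 | strongly unequal | 15.10 | 4.40 | 6.12 | 4.54 |

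Over all scenarios with ICC > 0:

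- Wald rejection is 9.8-15.1%, so the 95% CI covers 84.9-90.2%. With ICC = 0, Wald rejection is 8.9-15.4%.
- The root-mean-square empirical SE is about 0.86-0.93 of the true SD.
- The generalised score test rejects at 3.0-5.1%.

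Both parts of the correction matter. With 25% exposed and ICC > 0, a corrected variance with a normal reference still rejects at 6.4-12.3%. An uncorrected variance with t5 gives 3.8-7.6%.

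**The case against.** **The P-value may be sound.** A reader might infer that chance differences will be called significant at two to three times the nominal rate. The protocol does not establish that. It fixes the standard error and judges significance by P-value, but does not say the P-value is a Wald test. Table 2 has one P per factor, including factors with several levels, so a Wald or a generalised score test would fit. Under a score test there is no inflation. This objection stands, and the error rate is conditional on the test. It does not rescue the interval.

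**Six may not be the full count.** Exposure is defined at the time of the stroke, while the list covers centres present throughout the study period. A municipality whose centre opened or closed between 1996 and 2006 would be exposed for part of the period and not listed. With 8 to 15 exposed municipalities (an assumption), Wald rejection was about 8-11%. So exactly six exposed municipalities, and a fixed 5 df, are inferences. The problem shrinks but remains.

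**The row is not primary.** A reader might treat municipality type as the study's main policy question. It is one of seven explanatory variables; calendar year is also motivated by policy reforms, and the stated use is to supply expected return-to-work proportions for comparison. The Discussion already bars a causal reading. This lowers the severity.

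**A condensed article may leave such detail to a fuller plan.** That is fair for the reference distribution, which is not stated; 1.96 is taken here as the usual companion of the empirical SE. The variance estimator is not left open, however: the article names it for the whole model.

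**Conclusion.** The point holds as a defect in one interval. For municipality type, a 95% CI from the uncorrected empirical SE with a normal reference covers about 85-90% when six municipalities are exposed. A Wald P-value would carry the matching 10-15% error. A score P-value would not, and could then contradict the CI printed beside it.

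The figures rest on assumed municipality numbers, sizes, exposed share and ICC. The cause is the small number of exposed municipalities: 98 and 275 in total gave similar results, and no scenario with six exposed restored 95% coverage.

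It does not follow that the model as a whole is unsound. The patient-level predictors vary within municipalities, and the self-employment power statement is correct. This should be fixed, but it does not threaten the study's main use.

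**What to change.** Keep the planned GEE for all other predictors. For the municipality-type row only:

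1. Take the CI and P-value from a small-sample-corrected sandwich variance (Kauermann-Carroll or Mancl-DeRouen) with a t reference whose degrees of freedom are the actual number of exposed municipalities minus one (5 if the six listed are all). A two-stage analysis of covariate-adjusted municipality log-odds with the same degrees of freedom is an equal alternative.
2. State whether the list of six is complete under the time-of-stroke definition, and report in Table 2 how many exposed municipalities carry the contrast.

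With six exposed municipalities, 25% of patients in them and ICC > 0, the simulated error was 2.8-6.1% with Kauermann-Carroll and 2.1-4.5% with Mancl-DeRouen.

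The cost is a sentence of text, a few lines of code and a wider interval for this variable. In the limiting case of six equal clusters that dominate the variance, the interval widens by a factor of (2.571/1.96) × √(6/5) ≈ 1.44 with Kauermann-Carroll, or (2.571/1.96) × 6/5 ≈ 1.57 with Mancl-DeRouen.
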